## Abstract

Recreational dance offers significant psychological well-being potential. However, traditional instruction emphasizes technique while limiting attention to nervous system development and embodied meaning-making. Despite empirical support for polyvagal theory, motor learning science, somatic education, and phenomenology, their systematic integration into unified structures is not clearly established in recreational dance contexts. This protocol integrates nervous system regulation, motor learning, and creative expression within structured Imperial Society of Teachers of Dancing (ISTD) modern dance syllabus for recreational adults. It presents a 12-week integrated dance-mindfulness intervention addressing this gap through a three-phase structure grounded in neuroscience and embodied pedagogy. The intervention comprises eight standardized components delivered weekly. The randomized controlled trial evaluates intervention effects using the Satisfaction With Life Scale (SWLS), Depression Anxiety Stress Scales-21 (DASS-21), the Mindful Attention Awareness Scale (MAAS), the Subjective Happiness Scale (SHS), and the Leisure Involvement Scale (LIS). Qualitative assessment via semi-structured phenomenological interviews (Weeks 8 and 12) and weekly journaling captures somatic awareness, nervous system resilience, technical confidence, creative expression, relational and social belonging, and embodied meaning-making. Intervention participants are expected to show significantly greater improvements compared to controls. Results will establish evidence-based practice standards for recreational dance and demonstrate neuroscience integration’s efficacy for psychological wellbeing and embodied meaning-making.

## 1. Introduction

### 1.1. Background

Recreational dance is a leisure-based movement activity. It is pursued primarily for intrinsic rewards including enjoyment, self-expression, social connection, and personal well-being, as distinguished from professional performance contexts or clinical therapeutic interventions [1,2]. Research confirms that dance interventions significantly enhance emotional regulation, reduce stress, and promote social integration in recreational adult dancers and other populations [1,3,4], while also serving as a neuroprotective activity demanding complex cognitive engagement. For those navigating psychological distress, conscious movement facilitates non-verbal emotional expression and fosters psychological safety [5].

Traditional dance instruction emphasizes proprioceptive awareness to guide and coordinate complex movements [6,7]. However, dancers often receive limited support for developing psychological awareness and holistic well-being competencies that support mental health [7]. This represents a critical gap in dance education: while dance can be a powerful medium for psychological health and embodied resilience, current training rarely integrates mental skills development with technical instruction. Research has identified the absence of standardized, integrated protocols combining these elements as a significant limitation in the field [3].

Polyvagal Theory [8,9] positions the autonomic nervous system as the foundation for social engagement and learning capacity through neuroception. Neuroception is the subconscious physiological detection and interpretation of environmental cues signaling safety or threat, independent of conscious appraisal. Neuroception operates automatically, influencing whether the nervous system moves toward social engagement or defensive dysregulation. While Polyvagal Theory has generated important insights into nervous system regulation, recent neuroscientific debate has raised questions regarding specific anatomical claims [9]. This protocol draws on PVT’s overarching framework of nervous system hierarchy and safety-based learning while remaining open to evolving neuroscientific understanding.

In dance education, the presence of a safe, co-regulated environment allows the nervous system to maintain a parasympathetic tone (ventral vagal state) while remaining capable of engaging sympathetic activation for movement without triggering dysregulation into threat states, which is a critical condition for creative expression and learning [8,10]. Evidence indicates that deliberate cultivation of the Social Engagement System (ventral vagal activation) optimizes nervous system flexibility—the organism’s capacity to dynamically regulate physiological arousal to meet environmental and task demands [9,11]. This flexibility creates conditions where technical development can occur without physiological distress or threat-based dysregulation.

Motor learning science demonstrates that dance technique mastery is enhanced when new motor information builds upon, and is compatible with, existing motor schemas, generalized rules, and parameters that guide motor behavior, thereby accelerating skill integration and transfer [12,13,14]. Achieving a state of flow (full task engagement with optimal challenge) depends on the balance between an individual’s skills and the perceived task difficulty [15,16]. However, to maintain flow while progressively increasing difficulty, the gradual titration of challenge must also consider nervous system capacity. Within neuroscience frameworks, this means ensuring participants remain within their window of tolerance, the optimal arousal zone where learning occurs without triggering threat-based defensive states [10,17], thereby avoiding both anxiety (hyperarousal) and boredom (hypoarousal), which inhibit functional learning.

Functional breathing re-education provides specific techniques for physiological regulation during movement. Practices such as nasal breathing and diaphragmatic activation assist in maintaining sympathovagal balance and supporting autonomic regulation [18]. Research on acute responses to exercise protocols demonstrates that affective experience and perceived exertion vary across different training modalities [19].

Body movement influences emotion regulation through multiple complementary mechanisms. First, physiological: intense, rhythmic movement triggers neurochemical changes in neurotransmitter (serotonin, dopamine), hormone (cortisol), and endocannabinoid levels, thereby reducing anxiety and depression [18]. Second, kinesthetic/somatic: deliberate, mindful modifications of movement quality such as weight distribution, postural adjustments, and breath-informed pacing enhance emotional states through embodied feedback loops and interoceptive awareness [18]. Third, neuropsychological: dance and music activities create flow states (full task engagement with reduced self-referential thinking) mediated by dopaminergic reward systems [20], while also enhancing creative expression, self-confidence, and social connection [21,22].

The central point to this integrated approach is “embodied learning” or “bodyfulness,” where the body is treated as the site of lived experience rather than just an instrument. This approach encourages somatic awareness and regulation, transforming dance into a holistic practice of psychological flexibility [2,3,5]. The phenomenological approach recognizes dance as a process of embodied meaning-making [23,24]. Phenomenology operates as an analytical framework that documents how participants experience neurological and kinesthetic changes during the protocol [25]. This process extends beyond individual development; according to interpersonal neurobiology theory, consciousness emerges as an embodied and relational phenomenon arising through interaction [10].

Within dance contexts, embodied self-awareness provides the foundation for developing reflective capacity. The body becomes the site where reflection originates, merged with empathic connection and fostering interpersonal presence [23]. Technical skill development does not occur in isolation but rather through sustained embodied reflection nested within collaborative movement, group improvisation, and reciprocal perspective-taking [25]. When participants engage in these relational movement experiences, where individuals retain their uniqueness while simultaneously participating in collective expression, learning is catalyzed by recognition of social interdependence and awareness that personal performance contributes to collective accomplishment [3,14]. Research on motor learning demonstrates that social-comparative feedback and collaborative contexts enhance both performance expectancies and learning outcomes [14]. Consequently, technical advancement, emotional resilience, and social integration develop synergistically within an integrated, embodied learning ecology through the coordinated engagement of individual expression, relational attunement and collective coherence [3,14].

Christensen et al. [1] identified six foundational components in recreational dance: rhythm and music, sociality, technique and fitness, connectedness, flow and mindfulness, and esthetic emotions. These components develop emotional regulation through complementary mechanisms like physiological (neurochemical shifts from rhythmic movement), kinesthetic-somatic (interoceptive awareness and embodied feedback), and neuropsychological (flow states and creative expression). Recreational dance, evaluated by how it “feels” rather than how it appears, naturally reduces stress and fosters authentic self-expression in supportive, non-competitive contexts [1]. Social synchrony through group movement engages mirror neuron systems and oxytocin-mediated bonding, while technique mastery demands complex cognitive integration. Critically, while these six components operate synergistically in lived recreational dance practice, current pedagogy rarely systematizes their intentional integration or monitors their psychological effects through rigorous empirical assessment [1].

Despite the potential of dance for well-being, the current literature reveals critical disconnects in pedagogical and neuroscientific application for recreational populations. Existing interventions lack cohesive theoretical frameworks that systematically operationalize neuroscience into dance pedagogy. As Zafeiroudi et al. [3] report, programs are often fragmented, lacking the ability to clearly bridge the gap between abstract somatic theory and concrete teaching methodology. Most concerning is the distinct lack of Randomized Controlled Trials (RCTs) targeting recreational dancers. Research predominantly focuses on clinical populations (therapy) or elite professionals (performance), leaving recreational dancers, who seek well-being and expression, without clear evidence-based guidelines [2,3]. Finally, the existing literature lacks phase-based pedagogical structures that respect the nervous system, progressing from safety establishment to optimal challenge while ensuring participants remain regulated throughout the learning process during dance class.

### 1.2. Aim and Objectives

The aim of this study is to develop and theoretically justify a comprehensive, 12-week integrated dance-mindfulness protocol grounded in polyvagal theory, motor learning science, and embodied phenomenology. The protocol systematically operationalizes the cultivation of nervous system resilience, technical dance competence, authentic creative expression, and social belonging within structured modern dance theater (Imperial Society of Teachers of Dancing-ISTD syllabus [26]) for community-based adult dancers. The study investigates whether this integrated protocol produces measurable psychological improvements compared to standard dance instruction, and whether participants report enhanced embodied meaning-making and somatic awareness through phenomenological accounts. The specific objectives are:(1)To develop and operationalize a comprehensive, 12-week integrated dance-mindfulness protocol grounded in neuroscience, motor learning, and embodied phenomenology that systematically integrates theory with practice.(2)To evaluate the protocol’s effectiveness using a mixed-methods RCT design comparing intervention and control groups on quantitative and qualitative outcomes.(3)To evaluate the intervention’s effectiveness on psychological well-being and embodied experience.

Based on the theoretical framework and structure of the 12-week intervention, it is hypothesized that participants in the dance mindfulness intervention group will demonstrate significantly greater improvements than those in the control group across primary quantitative outcomes (life satisfaction, subjective happiness, psychological distress, mindful attentional capacity, and leisure involvement) and secondary qualitative outcomes (enhanced somatic awareness, nervous system resilience, technical confidence, creative expression, relational belonging, social connection and embodied meaning-making).

The present protocol is designed for community-based, non-clinical recreational dance classes rather than as a therapeutic program for trauma or other clinical mental health conditions. It targets healthy adult recreational dancers and focuses on supporting everyday psychological wellbeing in the context of regular dance classes. The pedagogical approach aims to foster nervous-system regulation to facilitate learning and flow while maintaining clear professional boundaries: instructors provide structured movement and mindfulness-based cues but do not deliver psychotherapy or intentionally explore traumatic material. If a participant experiences significant emotional distress during a session, their participation in that session is paused and they are referred to external mental health professionals for appropriate clinical support.

## 2. Experimental Design

### 2.1. Trial Design

This study has been prospectively registered on ClinicalTrials.gov (NCT07262177; brief title: Dance-Mindfulness Intervention for Well-Being in Recreational Adults-DanceMind) and approved by the institutional Research Ethics Committee (IEC, DPESS, UTH 4-2/2.4.2025; Supplementary File S8 [27]). The protocol follows SPIRIT [28,29], TIDieR [30], and CONSORT standards [31].

This is a two-parallel group randomized controlled trial (RCT). The intervention group receives a 12-week integrated dance-mindfulness protocol grounded in polyvagal theory, motor learning science, and embodied phenomenology. The control group continues regular recreational dance activities without mindfulness or somatic-reflective components. Participants are randomly allocated 2:1 (intervention: control) using computer-generated randomization with allocation concealment.

Quantitative assessments occur at baseline (T0) and post-intervention (T2 Week 12). Qualitative data collection occurs at mid-intervention (T1 Week 8) and post-intervention (T2 Week 12). This mixed-methods design permits concurrent testing of quantitative psychological outcomes (life satisfaction, subjective happiness, psychological distress, mindful attention, leisure involvement) and qualitative embodied experiences (somatic awareness, nervous system resilience, technical confidence, creative expression, relational belonging, meaning-making).

All procedures follow ethical principles outlined in the Declaration of Helsinki. Written informed consent is obtained prior to enrollment. Participants have the right to withdraw at any time without consequence. Personal data are stored securely in encrypted databases. Each participant receives a unique study code; identifying information is separated from research data. All facilitators hold CPR/First Aid certification and mindfulness training. Session checklists document adverse events. If a participant reports intense psychological distress, the study is suspended for that individual with clinical referral provided. Facilitators are trained to recognize signs of emotional dysregulation and provide immediate basic containment (quiet space, grounding breath), without attempting psychological exploration. Control group participants receive delayed access to the intervention after post-intervention assessment (Supplementary Files S1–S8 [27]).

### 2.2. Study Setting

The study will be conducted across private dance schools in Thessaly, Greece. All baseline (T0) and post-intervention (T2) quantitative assessments will be held in quiet, standardized studio environments at each participating dance school to ensure ecological validity and participant accessibility. All qualitative interviews (T1 Week 8, T2 Week 12) will be conducted in private, quiet locations at the respective dance schools. The 12-week dance-mindfulness intervention will be delivered at the designated dance studios in Thessaly region in Greece. Each studio meets the standardized environmental specifications to ensure consistent and safe delivery across sites (Supplementary File S2 [27]).

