Site coordinators maintain a screening log documenting all preliminary screening contacts, including date of screening, recruitment source, preliminary eligibility status (age, dance experience, attendance availability, language fluency), exclusion criteria met (if applicable, specifying which criterion 1–6), clearance documentation status, and disposition (enrolled in baseline assessment, not meeting criteria, awaiting clearance). This log enables complete CONSORT [31] flowchart documentation and allows identification of potential selection bias or recruitment barriers. In the event that randomized participants withdraw or fail to meet attendance criteria (≤70% of sessions), they are retained in all analyses using intention-to-treat methodology. Missing outcome data will be addressed through multiple imputation or last-observation-carried-forward approaches, as appropriate based on data missingness patterns. Replacement participants are not recruited mid-trial, as this would create methodological complications (unbalanced final sample size, potential confounding from replacement timing differences). Final sample size analyzed may differ from target sample size and will be fully documented in the CONSORT compliant participant flowchart, which will be generated upon study completion detailing actual enrollment, randomization, and attrition data by group and reason for withdrawal.

All participants provide written informed consent prior to baseline enrollment. Personal data are handled in strict compliance with the General Data Protection Regulation. All participant identifiers are replaced with unique numeric codes; codebooks linking codes to identifying information are encrypted and stored separately from all research data, accessible only to the principal investigator. Paper materials are stored in locked filing cabinets in restricted-access laboratory space; digital data are stored on secure, password-protected institutional servers with automated daily backups. Data are retained for five years following study completion; paper documents are shredded, and digital data securely deleted thereafter, in accordance with institutional policies and GDPR regulations.

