### 2.7. Data Collection and Analysis

Self-report questionnaires (SWLS, DASS-21, MAAS, SHS, LIS) are administered on paper at baseline (T0) and post-intervention (T2) by trained site coordinators in quiet studio environments (~20–30 min per assessment). Questionnaires are entered into a secure electronic database with double-entry verification.

Demographic and baseline characteristics are summarized using descriptive statistics (means, standard deviations, medians, frequencies, percentages). Shapiro–Wilk tests and visual inspection (Q-Q plots, histograms) assess normality for all primary outcome variables. Between-group demographic comparisons use independent-samples *t*-tests (continuous) and chi-square tests (categorical). Internal consistency is assessed using Cronbach’s alpha (α ≥ 0.70); test–retest reliability via intraclass correlation coefficients (ICC ≥ 0.70) in the control group.

If normality is met (Shapiro–Wilk *p* > 0.05), a 2 (Group) × 2 (Time) mixed-model repeated-measures ANOVA is conducted on each primary outcome, with Bonferroni-corrected α = 0.01 to control Type I error. Alternative testing via MANOVA (Wilks’ Lambda, α = 0.05) proceeds to univariate ANOVAs if significant. ANCOVA with T0 baseline covariates is conducted with Levene’s test assessing homogeneity of variance; if violated (*p* < 0.05). Effect sizes and 95% confidence intervals are reported.

If normality is violated (Shapiro–Wilk *p* < 0.05), non-parametric tests will be used: Friedman’s test (within-group time effects), Mann–Whitney U (between-group comparisons), Wilcoxon signed-rank test (within-group pre–post). Post hoc pairwise comparisons use Bonferroni-corrected alpha. Pearson correlations (Bonferroni-corrected) for normally distributed variables; Spearman’s rank-order correlations for non-normal variables. Correlations ≥ |0.30| are highlighted. Quantitative analyses use IBM SPSS v. 28; results are reported per CONSORT guidelines [31] with summary statistics, 95% confidence intervals, and effect sizes. Significance level: α = 0.05 (two-tailed) unless otherwise specified (Bonferroni-corrected α = 0.01).

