### 3.2. Data Collection

Quantitative outcome measures (described in Section 2.5) are administered on paper at baseline (T0) and post-intervention (T2, Week 12). Post-intervention assessments are conducted by trained coordinators/assessors blinded to group allocation; blinding is maintained by: (1) providing assessors only the participant study code (no group information); (2) restricting assessor access to baseline data or randomization records; and (3) ensuring assessors have no knowledge of intervention attendance or session fidelity ratings. Completed questionnaires are entered into a secure electronic with double-entry verification. Missing data patterns are examined; Section 2.7 specifies handling strategies.

Weekly Journaling (Intervention Group Only): Intervention group participants complete standardized written reflections (5–10 min) at the end of each session using prompts addressing: breath/embodiment, emotional states, movement awareness, meaning-making, and perceived changes across weeks (prompts detailed in Supplementary File S3 [27]). Journal forms are collected weekly by facilitators and maintained in secure storage. A purposive sample of journal entries (selected from Weeks 1, 4, 8, and 12, plus entries with maximum phenomenological variation) is analyzed for thematic patterns regarding embodied experience, affective change, and perceived transformation using Reflexive Thematic Analysis with phase-specific coding (Weeks 1–4, 5–8, 9–12; detailed methodology in Supplementary File S3 [27]). Two independent coders will analyze qualitative data using structured coding protocols; differences are resolved through consensus discussion. Control group participants do not complete journaling; they complete quantitative assessments only (T0 and T2).

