### 3.7. Post-Intervention Assessment (T2, Week 12)

At Week 12, all randomized participants complete the final assessment to evaluate intervention outcomes and longitudinal progression. Both intervention and control groups complete the identical battery of five outcome measures administered at baseline (T0), following standard administration procedures to ensure comparability. The same subsample of participants interviewed at T1 completes a second semi-structured interview (20–30 min). The T2 guide (Supplementary File S3) [27] retains the core phenomenological domains but pivots the inquiry toward integration and transformation. Participants reflect on their trajectory across the full 12-week period, enabling an analysis that compares T1 (midpoint) and T2 (endpoint) narratives to map the developmental arc from early somatic grounding to late-phase creative expression.

Intervention participants complete a final journal entry (Supplementary File S3) [27] specifically designed to export a retrospective comparison between their Week 1 and Week 12 embodied states. This completes the qualitative dataset, which is then stratified into three Phase-aligned segments (Weeks 1–4, 5–8, 9–12) for Reflexive Thematic Analysis (coding framework detailed in Supplementary File S3 [27]).

The qualitative strategy at T2 focuses on triangulation: phase-specific journal themes are cross-referenced with longitudinal interview narratives to construct a mechanistic explanation of embodied change. Control group participants complete only the quantitative assessment, preserving the distinction between outcome evaluation (quantitative/comparative) and process evaluation (qualitative/descriptive).

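### The only stated route for the Week 12 self-report forms is a supervised paper session at the dance school, with no fallback for people who have stopped attending but stay in the intention-to-treat analysis

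*Protocol article*

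**What the plan says.** Place and mode of the quantitative assessments are fixed in three sections of the protocol article.

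- Section 2.2: "All baseline (T0) and post-intervention (T2) quantitative assessments will be held in quiet, standardized studio environments at each participating dance school". The reasons given there are ecological validity and accessibility for participants.
- Section 2.7: the five questionnaires (SWLS, DASS-21, MAAS, SHS, LIS) "are administered on paper at baseline (T0) and post-intervention (T2) by trained site coordinators in quiet studio environments", taking about 20–30 minutes.
- Section 3.2 repeats paper for T0 and T2 and names no other mode.

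Other sections set out whose T2 data are needed.

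- Section 3.7: "At Week 12, all randomized participants complete the final assessment".
- Section 2.4 foresees that "randomized participants withdraw or fail to meet attendance criteria" may apply to some people and says "they are retained in all analyses using intention-to-treat methodology". It expects missing outcomes, to be handled by multiple imputation (MI) or last observation carried forward (LOCF), and rules out replacement.
- Section 3.5 has coordinators contact people who miss sessions. The stated purpose is make-up sessions and barriers to attendance, not collection of outcome forms.

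**The concern.** The analysis needs Week 12 values from people who have left the classes, but the only route for obtaining them is a return to a participating dance school. All five primary outcomes are short self-report forms, and nothing in the instruments requires a studio or a supervisor.

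Someone who left because of dissatisfaction, distress or lack of benefit is less likely to go back to the place they left. Missingness may then be related to the outcome. It may also be unequal between arms: intervention participants have a new 12-week programme to leave, while controls continue classes of their own preference and are promised the programme free of charge after T2. At stake are the validity of all five primary contrasts and some precision, in a trial that does not replace losses.

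**Working it through.** **Inputs.** From Section 2.4: d = 0.50, α = 0.05, power 0.80, 76 intervention and 38 control participants, no stated allowance for dropout. From Section 2.7: two-tailed testing, with a Bonferroni-corrected α = 0.01 for each primary outcome. The article gives no attrition rate, so every loss rate and every difference between leavers and completers below is an assumption.

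**The plan's own figure.** A two-sample comparison with 2:1 allocation, one-sided α = 0.05, power 0.80 and no dropout gives 38 + 76 = 114 (exact t power 0.804). A two-sided 0.05 test would need 48 + 96 = 144. So 114 is reproduced only with every T2 form in hand.

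**Shift in a completer contrast.** Let a share q of an arm be missing, with leavers worse than completers by g SD. The completer mean then exceeds the full-arm mean by q × g, and the between-arm contrast shifts by (q_I − q_C) × g. Assume q_I = 0.20 and q_C = 0.10:

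- g = 0.5: 0.10 × 0.5 = 0.05 SD
- g = 1.0: 0.10 × 1.0 = 0.10 SD

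That is 10–20% of the planned effect of 0.50 SD. With equal loss in the two arms and the same g, this shift is zero.

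**If half of the missing forms come back**, and those who return them are typical of the leavers, the shift per arm becomes g × [q − (q/2)/(1 − q/2)]:

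- intervention: 0.20 − 0.10/0.90 = 0.089
- control: 0.10 − 0.05/0.95 = 0.047
- difference: about 0.042 × g, or 0.02–0.04 SD

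**Under the planned handling.** With quantitative outcomes only at T0 and T2, LOCF sets each leaver's change to zero. If the leavers' true mean changes are c_I and c_C, the contrast in change is off by −(q_I × c_I − q_C × c_C). The sign depends on what happened to the leavers: a decline among intervention leavers is hidden, and an improvement is discarded. MI predicts a leaver's T2 from T0 and from the completers, so it cannot recover a departure that arose after baseline.

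**Precision.** Noncentral t, d = 0.5, two-sided α = 0.01. Forms missing: 76 × 0.80 ≈ 61 and 38 × 0.90 ≈ 34 remain. Half recovered: 76 × 0.90 ≈ 68 and 38 × 0.95 ≈ 36 remain. The last column is baseline-adjusted, with an assumed T0–T2 correlation of 0.5, so d becomes 0.5/√(1 − 0.25) = 0.577.

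| Analysed (intervention/control) | Total | Power, unadjusted | Power, ANCOVA |
|---|---|---|---|
| 76/38 | 114 | 46% | 61% |
| 61/34 | 95 | 39% | 53% |
| 68/36 | 104 | 42% | 57% |

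Recovering half of the missing forms regains about 4 points on either basis (0.389 to 0.425 unadjusted; 0.529 to 0.571 adjusted).

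**Other loss rates.** Equal loss of 10%, 20% or 30% in both arms takes unadjusted power at two-sided 0.01 from 46% to 41%, 36% and 30%.

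**The case against.** The strongest reply is that this is a journal article. Section 3 calls itself an overview and refers to supplementary files for full procedures, so a fallback for missed visits could sit there. Silence alone would indeed be no finding. But Section 2.2 is not silent: it places all T2 assessments in the studio, and Sections 2.7 and 3.2 repeat the mode. The point is about that stated rule.

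A reader might infer that the plan makes having an outcome conditional on continued attendance, or that leavers are certain to be lost. The documents do not support either reading. T2 is a single visit, separate from the sessions. Section 2.3 lists commitment to the assessments apart from commitment to 70% of sessions. Section 3.7 intends full ascertainment, and Section 3.5 keeps contact with absentees and offers help with childcare, transport and scheduling. Loss of leavers is an inferred risk.

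It is also fair that Section 2.2 chose the studio for accessibility. That reason fits people who still come to classes; it is weaker for those who have left.

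A further objection is that the completer shift describes an analysis the plan does not specify. This stands: with MI or LOCF the size and direction may differ, so the figures do not show a bias in favour of the programme. The low starting power is also a separate matter, because the trial was sized at 0.05 and tests at 0.01.

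Finally, off-site forms mix modes, probably mostly among non-adherers, so mode would be tied to adherence and perhaps to arm. A sensitivity analysis that drops those forms would largely recreate the completer analysis. Both points are fair and shape the fix. People who withdraw from the study altogether may not answer by any route.

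**Conclusion.** The point holds as a design weakness that is cheap to remove. The plan asks for T2 from everyone randomised and analyses by intention to treat, but states a single collection route that is hardest for the people most likely to be missing. It is not a contradiction in the text, and it does not show that the results will be biased or which way.

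The illustrated size is modest: 0.05–0.10 SD in a completer contrast, and about 4 power points regained per primary outcome. Both rest on assumed losses of 20% and 10%; the shift also assumes leavers 0.5–1.0 SD worse, and the adjusted power a correlation of 0.5. The main gain from a second route is fewer imputed outcomes among leavers, where two time points give imputation little to work with.

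**What to change.** Keep the supervised studio session as the default and amend Sections 2.2, 2.7, 3.2 and 3.7 as follows:

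- Anyone who misses the T2 visit and has not withdrawn consent for data collection is sent the same five questionnaires by post or secure link.
- The forms are to be returned within a short window fixed in advance and, for controls, before delayed access to the programme begins.
- Returned forms enter the primary intention-to-treat analysis.
- The mode of completion is recorded and reported by arm.

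The cost is postage or an online form and a minor amendment. No outcome, treatment or sample size changes. The downside is a few forms completed in a less standardised setting and a different mode, which is preferable to having no outcome from those participants.
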